## Abstract

**Background:**

The trial addresses the general question of whether community resource centers run by a non-government organization improve the health of women and children in slums. The resource centers will be run by the Society for Nutrition, Education and Health Action, and the trial will evaluate their effects on a series of public health indicators. Each resource center will be located in a vulnerable Mumbai slum area and will serve as a base for salaried community workers, supervised by officers and coordinators, to organize the collection and dissemination of health information, provision of services, home visits to identify and counsel families at risk, referral of individuals and families to appropriate services and support for their access, meetings of community members and providers, and events and campaigns on health issues.

**Methods/design:**

A cluster randomized controlled trial in which 20 urban slum areas with resource centers are compared with 20 control areas. Each cluster will contain approximately 600 households and randomized allocation will be in three blocked phases, of 12, 12 and 16 clusters. Any resident of an intervention cluster will be able to participate in the intervention, but the resource centers will target women and children, particularly women of reproductive age and children under 5.

The outcomes will be assessed through a household census after 2 years of resource center operations. The primary outcomes are unmet need for family planning in women aged 15 to 49 years, proportion of children under 5 years of age not fully immunized for their ages, and proportion of children under 5 years of age with weight for height less than 2 standard deviations below the median for age and sex. Secondary outcomes describe adolescent pregnancies, home deliveries, receipt of conditional cash transfers for institutional delivery, other childhood anthropometric indices, use of public sector health and nutrition services, indices of infant and young child feeding, and consultation for violence against women and children.

**Trial registration:**

ISRCTN Register: ISRCTN56183183

Clinical Trials Registry of India: CTRI/2012/09/003004

## Background

### Rationale

A recent review of developments in urban health over the last 30 years identified four perceptual shifts [1]. First, more than health service inputs are necessary to improve health. Of particular interest are community participation and formation of partnerships with community-based organizations. Second, the emphasis should shift from individuals to communities. Third, there was a growing interest in multi-level determinants of health, including work on poverty, social interactions, the physical environment and services. Fourth, initiatives must go beyond the public sector. Informal settlement communities are heterogeneous [2,3], and health care often involves the private and informal sectors [4-7].

The Society for Nutrition, Education and Health Action (SNEHA), a Mumbai-based non-government organization (NGO), works to improve the health of women and children in disadvantaged communities. We have addressed health care from two directions: on the demand side, by attempting to create informed users of health services who expect higher quality; and on the supply side, by working with public sector health providers (in our city, the Municipal Corporation of Greater Mumbai) to improve the quality of health services [8].

A National Urban Health Mission (NUHM) is due to merge with the existing National Rural Health Mission of the Government of India. It seeks to address the health care needs of the rapidly growing urban population, with a focus on the disadvantaged. A significant change in the proposed strategies is a move from the provider perspective to a more collaborative approach. There is an emphasis on building local capacity and engaging communities in delivery of health care, and on building public-private partnerships to enhance quality of care. Any potentially scalable intervention should fit the National Health Mission agenda: training of link-workers and women’s health committees to carry out community health promotion activities, strengthening linkages between service providers and the community, especially vulnerable groups, regular outreach services to address low access by disadvantaged groups, and public-private partnership.

We have become interested in the potential of community resource centers as nexuses for improving family and community health. There is a tradition of NGOs basing their community work at local resource centers. In some cases the NGOs are small and the resource centers are their headquarters. In others, they are satellite nodes linked with larger central offices: the structural arrangement we aim to test. We estimate that there are about 60 major NGOs working on urban informal settlement development in Mumbai. Prominent groups, including Society for Promotion of Area Resource Centres (http://www.sparcindia.org), Akanksha Foundation (http://www.akanksha.org), Apnalaya (http://www.apnalaya.org), DoorstepSchool (http://www.doorstepschool.org) and Pratham (http://www.pratham.org), have run local community resource centers since the 1980s. These have served purposes as varied as provision of preschool, non-formal and remedial education, vocational training, recreation activities (*khelwadis*), health clinics, care centers for people with disabilities, family counseling, collective savings and loans, and physical space for community interaction. Some organizations, including Apnalaya, Stree Hitkarni, Committed Communities Development Trust (http://www.ccdtrust.org), and Navjeevan (http://www.navjeevan.org), have focused on community health. Their resource centers occupy a range of locations: individual homes, leased spaces, or sites provided by community-based organizations. They are staffed by a combination of volunteers and salaried cadres and are open from 8 to 24 hours daily.

Our previous trial of community mobilization through women’s groups suggested that women were eminently able to articulate their experiences, identify problems and suggest local solutions, but that they hit a wall when they tried to move to community action [9]. To some degree this is a feature of what we call the urban paradox: despite the density of informal settlement populations, contact with people outside one’s immediate area, cultural or kinship group is limited. While women’s groups in rural areas seem to be able to pull together communities for collective action [10,11], groups in urban informal settlements - though probably less poor and more ‘modern’ - often feel that they lack the power to push their agendas with neighbors and health-care providers.

Our idea is that satellite resource centers located in vulnerable areas could be formalized sources of health information and bases for community outreach work. Workers at each center will be members of the SNEHA team, backed by the experience, knowledge, connections and skills of project coordinators and directors: a decentralization in the non-government sector that answers calls for decentralization in the government sector. Information, training, awareness and advocacy events will be cascaded out through the resource centers. The centers will coordinate services such as community-based contraceptive distribution, outreach camps for immunization, counseling services for women facing violence, and day care with supplementary nutrition for malnourished children.

### Aims

Our propositions are that: (i) on the basis of our experience in community mobilization for health, we would like to move to a decentralized community resource center model; (ii) for feasibility given our expertise, we will limit both the intervention and its evaluation to health issues; (iii) although the model is a common one with many potential benefits, we have equipoise on its effect on population health; (iv) we would like to evaluate the model on the basis of outcomes designed to be unambiguous, commonly measured, externally comparable and representative of women’s and children’s health.

## Methods/design

### Setting

The capital of Maharashtra state, Mumbai has a provisional 2011 census population of 12.5 million [12], more than half of whom live in slums. About one-fifth of slum homes have a private toilet, 31% of residents have completed 10 years of education, and the total fertility rate is below the replacement threshold at 1.9 [13]. Public sector care is provided by the Municipal Corporation. Private health care is widely available and ranges from specialty hospitals to informal practitioners. The trial will be conducted in two of the city’s twenty-four municipal wards, each of which has a population of about 700,000, chosen on the basis of poorer human development ranking and a high proportion of slum settlements.

### Trial design

The study is a cluster randomized controlled trial in which 20 slum areas will be allocated to have community resource centers and 20 will act as controls. Allocation will be done in three blocks, of 12, 12 and 16 clusters, in a phased design with 6-month intervals between the start of each phase (Figure 1). It has been our experience that, in large cluster randomized controlled trials, instituting interventions simultaneously in all clusters is problematic. The phased design is logistically feasible and, we hope, will allow clear demarcation of intervention start times. We will conduct two rounds of data collection: a baseline census and a census after 2 years of intervention, in which the information is provided mainly by married women aged 15 to 49 years.

**Figure 1 F1:**
[figure not shown]
**Trial design.** DMC, data monitoring committee.

### Cluster size and selection

The sample frame will include clusters of approximately 600 households. Where settlements are large, we will divide them into smaller clusters along obvious physical boundaries. One large area may then provide more than one potential trial cluster, but we will try to avoid contiguity to minimize contamination. We think that the likelihood of contamination is limited both because of the urban paradox and because this has been our experience in previous projects. The distribution of vulnerability is not random and we will be able to define a sample frame within particularly deprived city wards. For example, areas in M-East ward are generally more vulnerable than others, with higher proportions of home births and higher mortality rates. The first step will be to identify the informal settlement areas in the chosen wards. This will be done by the data collection team, using their existing knowledge and inputs from the Municipal Corporation, the Tata Institute of Social Sciences, NGOs, and local key informants. The sample for each phase will be based on vulnerability scores derived from a rapid assessment tool [14].

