### Sample size

Based on the phase 1 baseline census in 12 clusters, we estimate that we will achieve interviews with 350 married women aged 15 to 49 years per cluster, and that we will have information on 80 pregnancies in the preceding 2 years, 80 children born in the preceding 2 years, and 120 children over 2 and under 5 years of age. We estimate that we will manage to measure the weights and heights of 150 children under 5 years of age per cluster. The sample size calculations assume two treatment groups, unmatched clusters of approximately equal size, and values of *k* (coefficient of variation of true proportions between clusters) equal in intervention and control groups [18]. Table 1 summarizes expectations for the primary outcomes. Control area proportions and values of *k* are based on the phase 1 baseline census in 12 clusters. The estimates were all made at 80% power. Because the intervention is part of our service delivery program, is of minimal risk, and will be evaluated after 2 years of operations, we are not specifying stopping rules.

**Table 1 T1:** Detectable differences in primary outcomes between allocation groups, with 40 clusters allocated 1:1, intervention:control

**Indicator**	**Estimated records per cluster**	***k***	**Control estimate (%)**	**Intervention estimate (%)**	**Detectable difference (%)**	**Detectable relative difference (%)**
Unmet need for family planning	350	0.11	46	41	−5	11
Incomplete basic immunizations in children under 5 years of age	160	0.22	66	53	−13	17
Weight-for-height >−2SD below median for age and sex in children under 5 years of age	150	0.1	20	16	−4	20

Records per cluster, *k*, and control estimate based on phase 1 data for 12 clusters. *k*, coefficient of variation of true proportions between clusters; SD, standard deviation.

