### Randomization

Clusters have been pre-randomized by number (by [name]), in blocks of 12, 12 and 16. The randomization plan was created on 25 July 2011 (http://www.randomization.com) using seed 11426, and stored securely. Project staff were not aware of the allocation during the process of consent for cluster inclusion.

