### Analysis plan

An analysis plan was discussed at the first meeting of the DMC in May 2012, and has been sealed. Presentation will follow the Consolidated Standards for the Reporting of Trials guidelines [20,21], beginning with a trial profile describing numbers of clusters, households, women and children enrolled in the evaluation, a summary of deviations from protocol, and a description of recruitment. Markers of identification will not be retained in analytical datasets. We will present a baseline comparison of allocation groups, summarizing household numbers, socioeconomic descriptors, including the Multidimensional Poverty Index [22], women’s age, education, and duration of residence, and numbers of births, and children under 2 and under 5 years of age. We will compare the primary outcomes between allocation arms, using data from the endline census after 2 years of intervention. Provided that distribution criteria are met, we will use logistic regression with a random effect for cluster [18], adjusted for phase (the second option being generalized estimating equations). We will enter each outcome as a dependent variable and allocation as a binary independent variable. If substantial baseline imbalances between allocation groups in demographic and socioeconomic characteristics are noted at the second DMC, we will include them as independent variables in multivariable models. If there are baseline imbalances in primary and secondary outcomes, we will model change in proportion between baseline and endline.

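### The primary model fixes only phase as a covariate; ward and cluster vulnerability score should be prespecified in it instead of depending on an undefined imbalance trigger

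*Protocol article*

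**What the plan says.** All references are to the protocol article.

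- **Setting:** "The trial will be conducted in two of the city’s twenty-four municipal wards". Both were chosen for poorer human development ranking and a high proportion of slum settlements. The number of clusters per ward is not given.
- **Cluster size and selection:** "The sample for each phase will be based on vulnerability scores derived from a rapid assessment tool". As an example of how vulnerability is distributed, this section adds that "areas in M-East ward are generally more vulnerable than others, with higher proportions of home births and higher mortality rates". Home delivery is a secondary outcome; mortality is not a trial outcome.
- **Randomization:** clusters were randomized "in blocks of 12, 12 and 16. The randomization plan was created on 25 July 2011". The blocks are the phases. No stratum for ward or score is named.
- **Analysis plan:** "we will use logistic regression with a random effect for cluster [18], adjusted for phase". Two conditional routes follow. Demographic and socioeconomic characteristics become covariates if the second data monitoring committee meeting notes substantial imbalance. Change from baseline to endline is modelled if primary and secondary outcomes are imbalanced at baseline. No threshold is given for either route, and neither ward nor score is named.

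**The concern.** Ward and vulnerability score are set by cluster selection, before the intervention starts, and the intervention cannot alter them. They are natural cluster-level covariates, and the protocol itself ties them to deprivation. The stated rule has two weaknesses.

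First, the content of the primary model stays open until someone judges whether an imbalance is substantial, and it is unclear whether ward or score counts as a demographic or socioeconomic characteristic. Second, an imbalance trigger targets only one of the two reasons for adjusting. A covariate that predicts the outcome reduces the residual between-cluster variance even when the arms are well balanced, and under this rule that gain is forgone in exactly that case.

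With 20 clusters per arm, between-cluster variance dominates two of the three primary comparisons, so the second weakness could matter.

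**Working it through.** **Inputs from Table 1 (Sample size section).** The table gives "Detectable differences in primary outcomes between allocation groups, with 40 clusters allocated 1:1, intervention:control", at 80% power.

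| Outcome | Records per cluster m | k | Control p0 | Intervention p1 |
|---|---|---|---|---|
| Unmet need | 350 | 0.11 | 0.46 | 0.41 |
| Incomplete immunization | 160 | 0.22 | 0.66 | 0.53 |
| Low weight-for-height | 150 | 0.10 | 0.20 | 0.16 |

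A two-sided 5% level is assumed because the article states none. Then (1.960 + 0.842)² = 7.849.

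**Step 1: reproduce the plan's figures.** The unmatched-cluster formula for proportions is

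c = 1 + 7.849 × [p0(1−p0)/m + p1(1−p1)/m + k²(p0² + p1²)] / (p0 − p1)²

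- Unmet need: within-cluster part 0.001401, between-cluster part 0.004594. c = 1 + 7.849 × 0.005995 / 0.0025 = 19.8, against 20 planned. Power is 0.804 and the detectable difference 4.98 points, so Table 1 is reproduced.
- Immunization: 0.002959 + 0.034679. c = 1 + 7.849 × 0.037638 / 0.0169 = 18.5. The detectable difference is 12.5 points (13 stated).
- Low weight-for-height: 0.001963 + 0.000656. c = 1 + 7.849 × 0.002619 / 0.0016 = 13.8. The detectable difference is 3.3 points (4 stated), so the table is conservative here.

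**Step 2: how much a cluster-level covariate can act on.** The between-cluster share of the variance is 0.004594/0.005995 = 77% for unmet need, 0.034679/0.037638 = 92% for immunization and 0.000656/0.002619 = 25% for low weight-for-height.

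**Step 3: effect of adjustment.** Replace k² by (1 − R²)k², where R² is the share of between-cluster variance that ward and score explain beyond phase. The documents give no R², so a range is assumed. This works on the proportion scale and only approximates the logistic model. Detectable difference with 20 clusters per arm, in points, with power at the Table 1 difference in brackets:

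| R² | Unmet need | Immunization | Low weight-for-height |
|---|---|---|---|
| 0 | 4.98 (0.804) | 12.5 (0.832) | 3.32 (0.926) |
| 0.2 | 4.59 (0.864) | 11.4 (0.899) | 3.24 (0.938) |
| 0.4 | 4.17 (0.922) | 10.1 (0.957) | 3.16 (0.949) |

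**Step 4: cost if the covariates explain nothing.** With 40 clusters, the intercept, allocation and two phase terms leave 36 cluster-level degrees of freedom; two more terms leave 34. The 5% critical t value moves from 2.028 to 2.032.

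**Step 5: chance ward imbalance under phase-only blocking.** In a block of N clusters, K of them in one ward, the number of that ward's clusters sent to intervention is hypergeometric with N/2 draws. Summing over blocks of 12, 12 and 16:

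| Assumed clusters of one ward per block | Arms differ by ≥4 of that ward's clusters | ≥6 | ≥8 |
|---|---|---|---|
| 6, 6, 8 (even split) | 0.36 | 0.12 | 0.03 |
| 8, 8, 10 | 0.33 | 0.10 | 0.02 |
| 12, 6, 2 (ward tracks phase) | 0.18 | 0.02 | 0.001 |

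With the even split, a difference of 4 is a 12:8 split and a difference of 6 is 13:7.

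**The case against.** The strongest reply is that nothing here is invalid. A random-effects model adjusted for the blocking factor is a sound analysis. The sample size assumes unmatched clusters and an unreduced k, so the stated power does not depend on further adjustment. A full covariate list is something an article commonly leaves to the analysis plan, and one exists, sealed and not shown. All of that stands. What remains is that the article itself states a rule making adjustment conditional on imbalance, and that rule can be judged as written.

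Four stronger readings are tempting, and the documents do not support them.

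- *Chance imbalance is left unadjusted.* The Analysis plan offers two conditional routes, including modelling change when baseline outcomes are imbalanced. Because the committee's second meeting reviews the baseline census, the covariate trigger also works on baseline data. The fair criticism is that it is undefined and conditional.
- *The protocol calls ward and score prognostic for the primary outcomes.* It links M-East to home births and mortality only, compares it with other areas in general, and does not say that it is one of the two trial wards.
- *Both variables were known for every cluster before allocation.* The list dates from 25 July 2011 and was made by cluster number, while scores are described phase by phase. The timing for later phases is not given. Adjustment does not need it: the score only has to predate the intervention.
- *The stated power is wrong without these terms.* It is not; step 1 supports it at the assumed 5% level.

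It is also fair that phase may already carry part of the score's variation, since the score drives each phase's sample. Table 1's k comes from phase 1 clusters alone, so it already describes within-phase spread.

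**Conclusion.** The point holds as a worthwhile improvement at almost no cost, not as an error in the plan. Phase is the only covariate certain to be in the primary model, and ward and vulnerability score could enter only through a trigger that has no threshold and does not name them.

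The possible benefit lies with unmet need and immunization: up to about 0.8 and 2.4 points off the detectable difference at R² = 0.4. For low weight-for-height it is negligible, under 0.2 points. Unmet need has the least spare power (0.804), so it is where a gain would be most useful.

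These sizes rest on an R² that the documents do not give, and at R² = 0 there is no gain. The 36% imbalance figure rests on an even ward split within phases and halves to 18% under the ward-tracks-phase scenario. The case for adjusting rests on the asymmetry: the loss is trivial if the variables turn out to be uninformative, and the gain is material if they are moderately informative.

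**What to change.** Leave the allocation list as it is. Before endline data are seen, add one sentence to the analysis plan: the primary model for each primary outcome includes ward and the cluster vulnerability score as fixed covariates alongside phase, whatever the observed baseline balance. State the form of each term; a binary term for ward and a linear term for the score use one degree of freedom each. The linear form should be checked against the scale of the score, which the article does not show. If the sealed plan already fixes these terms, the sponsor need only confirm it.

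The cost is that sentence and two cluster-level degrees of freedom. Ward needs no new data. The score should already be held from cluster selection, and this should be confirmed for all 40 clusters.

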### Participants

Although any resident will be able to participate in the intervention, the resource centers will target women and children, particularly women of reproductive age and children under 5 years of age. Evaluation will be based largely on interviews with married women aged 15 to 49 years.

